### **2.2.2 Secondary Endpoints**

1. Uterine vascular perfusion

1. Vasculature and extracellular matrix (ECM content of fibroids)

3. Whether (a) reduction of blood flow of uterine and fibroid vasculature and (b) shrinkage of fibroid depends upon subject being hypoestrogenic.

NB. The study aims to establish feasibility and reproduce ability of novel MR imaging techniques in the evaluation of treatment response in women with uterine fibroids. Hence there is not an efficacy measurement required for any of the drug treatment options.

# **STUDY DESIGN**

## **3.1 OVERALL STUDY DESIGN AND PLAN**

**Also see Charts – Appendix 4**

**PILOT Groups:**

Prior to commencement of the Open Investigational study (detailed below) we will refine our novel MRI technical evaluations of volumetric measurements and perfusion imaging.

**Pilot Group A -**

We wish to study up to 15 women already scheduled for hysterectomy who are, as part of routine management, going to receive a GnRH agonist prior to their planned surgery. The hysterectomy will be performed 21-28 days from the last dose of GnRH agonist. The GnRH agonists will be given 28+/-3 days apart. .

After successful screening and Ultrasound

On TWO occasions, these being - prior to the patient receiving the GnRH agonist and pre-hysterectomy after 2 or 3 months on GnRH agonist therapy, we will perform:

(i) Novel 1.5T MR imaging (including structural, dynamic contrast and magnetization transfer imaging)

On up to TWO occasions, these being - prior to the patient receiving the GnRH agonist and pre-hysterectomy after 2 or 3 months on GnRH agonist therapy, we will perform:

(ii) Doppler Ultrasound scanning. If Visit 1 falls within 28days of screening then the screening scan will remain valid. If this is anticipated then Dopplers will be carried out at screening.

Once the uterus is removed at hysterectomy the uterus will

(iii) also be studied in a novel way in the higher resolution 7T MR scanner and observations correlated with the histo-morphological examination of the uterus.

Blood samples will be taken on 3 occasions - at Screening and Day 28 to assess Urea and Electrolytes (U&E's), Full Blood Count (FBC), and Liver Function Tests (LFT's) and on the day of Hysterectomy (Visit 3) to assess, as before, plus Oestradiol (E), Progesterone(P), Luteinising Hormone (LH) and Follicle Stimulating Hormone (FSH) These blood samples will be taken on scheduled study visits to the hospital.

**Pilot Group B -**

We will recruit up to 15 women already scheduled for hysterectomy who will not be receiving a GnRH agonist prior to planned surgery as part of their routine clinical management.

After successful screening and Ultrasound -

On ONE occasion, within 10 days of their scheduled hysterectomy we will perform:

(i) Novel 1.5T MR imaging (including structural, dynamic contrast and magnetization transfer imaging.

(ii) Doppler Ultrasound scanning. If Visit 1 falls within 28days of screening then the screening scan will remain valid. If this is anticipated then Dopplers will be carried out at screening.

Once the uterus is removed at hysterectomy the uterus will

(iii) also be studied in a novel way in the higher resolution 7T MR scanner and observations correlated with the histo-morphological examination of the uterus.

Blood samples will be taken on 2 occasions - at Screening to assess Urea and Electrolytes (U&E's), Full Blood Count (FBC), and Liver Function Tests (LFT's) and on the day of Hysterectomy (Visit 2) to assess as before plus Oestradiol (E), Progesterone(P), Luteinising Hormone (LH) and Follicle Stimulating Hormone (FSH). These blood samples will be taken on scheduled study visits to the hospital.

-Pilot Group C

We will recruit up to 5 women already scheduled for hysterectomy who will not be receiving a GnRH agonist prior to planned surgery as part of their routine clinical management.

After successful screening and Ultrasound -

On ONE occasion, within 10 days of their scheduled hysterectomy we will perform:

1. Novel 1.5T MR imaging (including structural, dynamic contrast and magnetization transfer imaging) on each patient
2. Novel 3T MR imaging on each patient
3. Doppler Ultrasound scanning. If Visit 1 falls within 28days of screening then the screening scan will remain valid. If this is anticipated then Dopplers will be carried out at screening.

Once the uterus is removed at hysterectomy the uterus will

(iv) also be studied in a novel way in the higher resolution 7T MR scanner and observations correlated with the histo-morphological examination of the uterus.

Blood samples will be taken on 2 occasions - at Screening to assess Urea and Electrolytes (U&E's), Full Blood Count (FBC), and Liver Function Tests (LFT's) and on the day of Hysterectomy (Visit 2) to assess as before plus Oestradiol (E), Progesterone(P), Luteinising Hormone (LH) and Follicle Stimulating Hormone (FSH). These blood samples will be taken on scheduled study visits to the hospital.

**Main Study:**

This will be an open investigational study. This study will be conducted in up to 30 women with uterine fibroids scheduled for hysterectomy. Patients will be allocated to 3 treatment groups (randomised). The randomisation scheme will be drawn up by an independent statistician, and the allocated treatment codes will be put into sealed consecutively numbered opaque envelopes. When a patient is randomised into the study, she will receive the treatment indicated in the next available envelope.

For approximately 12 weeks (Groups 1 and 3) and approximately 13 weeks (Group 2) prior to surgery (hysterectomy) the participants will receive one of 3 possible treatment options:

Group 1 n=10: a monthly sub-cutaneous injection of a GnRH agonist [Goserlin 3.6mg] (total of 3 injections) commencing from day 1-5 of menstrual cycle

Group 2 n=10: a GnRH antagonist [sub-cutaneous injection of Cetrorelix 3mg] given on 3 occasions (Day 1, 4 & 7 +/- 1 day) commencing day 1 to 5 of the menstrual cycle with a GnRH agonist (Goserelin 3.6mgs) thereafter monthly for 3 months, commencing day 7+/- 1 day.

Group 3 n =10: A control group of women with fibroids (no medication). Day 1 of the study will be a specified day between day 1 to 5 of their menstrual cycle.

NB – Monthly is defined by 28 days +/-3 days.

The hysterectomy will be performed 21-28 days from the last dose of GnRH agonist. The GnRH agonists can be given 28+/- 3 days apart. The GnRH analogue, Goserelin 3.6mg subcutaneous, and the 2nd and 3rd doses of cetrorelix 3mg subcutaneous, can be administered in the patients’ own homes if more convenient. However, dose one of cetrorelix must be given in the hospital with the patient observed for 30minutes after the drug is administered.

**3.1.2 Measurements:**

Comparisons will be made between the following imaging modalities:

1. Sonographic assessment, colour Doppler imaging.
2. 1.5T MR imaging, including structural, dynamic contrast and magnetization transfer imaging.
3. Ex-vivo imaging with 7T MR scanner correlated with uterine histo-morphology.

For imaging exercises there will be one record per patient for each measurement at each time-point. The largest fibroid will be selected and total uterine volume measured.

It is not possible to have patients “blinded” to treatment option. It will be possible for the statistician, pathologists, radiologists, technicians and non clinical staff to be “blinded” to the treatment allocation, to the results of previous time-points, and to the results of other measures at the same time-point.

Following successful screening procedures all the participants will have a further 5 visits to the RIE.

On each of the visits 1 to 4 every participant will have a MRI, Ultrasound and Doppler. If Visit 1 falls within 28days of screening then the screening scan will remain valid. If this is anticipated then Dopplers will be carried out at screening.

Visit 1 will be carried out prior to randomisation (Within 28 days of Day 1)

Visit 2 at 14 days+/- 3 days following commencement of treatment

Visit 3 at 28 days+/- 3 days following commencement of treatment

Visit 4 Within 10 days prior to scheduled hysterectomy

Visit 5 Day of Hysterectomy and Ex-vivo imaging with 7T MR scanner of uterus

Blood samples will be taken on 3 occasions - at Screening, Day 28+/- 3 days (Visit 3)and on the day of Hysterectomy (Visit 5) to assess Urea and Electrolytes (U&E's), Full Blood Count (FBC), and Liver Function Tests (LFT's). These blood samples will be taken on scheduled study visits to the hospital.

A 10ml blood sample will be obtained on 11 occasions (Group 2) and 10 occasions (Groups 1 & 3) to obtain an estimate of Oestradiol (E), Progesterone(P), Luteinising Hormone (LH) and Follicle Stimulating Hormone (FSH). A small aliquot of blood will be stored in the freezer in reserve in case of any laboratory processing difficulties.

Some of these blood samples will be taken at the RIE when they coincide with Scheduled Study Visits. The participants will be given the option to have the rest of the blood samples taken in their own home if this is more convenient to them.

From Visit 1 all participants in the Main Study will be asked to collect 5mls of urine twice weekly and store frozen in their freezer at home. These will be collected on a regular basis by research staff.

In addition, a daily menstrual diary to record bleeding patterns throughout the study, commencing from Visit 1, until day of hysterectomy (Visit 5), will be completed by participants.

The study will be conducted on an inpatient basis on the day of hysterectomy and therefore, the majority of visits will be on an outpatient basis in the setting of the Edinburgh Royal Infirmary and other NHS Lothian Gynaecology Services or in the participant’s home if more convenient.

## **3.2 STUDY DURATION**

Up to 30 patients will be enrolled in the randomised study and up to 35 patients will be enrolled in the pilot study. For women recruited, the accrual period will be approximately 24 months. The study duration for each randomised patient includes a screening visit followed by 5 further visits over a total time period of up to 20 weeks. The study duration for each pilot patient includes a screening visit followed by up to 3 further visits over a total time period of up to 20 weeks.

## **3.3 CRITERIA FOR STUDY DISCONTINUATION**

The progress of this study will be assessed by The University of Edinburgh/NHS Lothian. The study may be discontinued for safety concerns.

## **3.4 DEFINITION OF END OF STUDY**

For the purposes of this study the “end of study” is defined as the day the last patient completes the last study visit.

# **STUDY POPULATION**

## **4.1 NUMBER OF PARTICIPANTS**

Up to 65 women.

## **4.2 INCLUSION CRITERIA**

Subjects must fulfil all of the following criteria:

### aged >18 years.

### Scheduled for hysterectomy with a fibroid uterus

### At least one intramural non-pedunculated, submucosal or subserous fibroid with a diameter of  2cm or multiple small fibroids with a uterine volume of  200cm3 confirmed by transvaginal or abdominal ultrasonography

### Normal cervical cytology within 3 years.

### Ability to understand and willingness to sign the informed consent form

## **4.3 EXCLUSION CRITERIA**

Subjects are to be excluded from the study if they meet any of the following criteria:

### Pregnant or lactating women

1. Contra-indication to magnetic resonance scanning
2. Unable to tolerate the supine position
3. Contra-indication to any of the medications to be utilized in study including gadolinium in contrast medium for MRI imaging
4. Diabetes and/or renal / hepatic impairment (eGFR<60mls/per min)
5. Known history of allergic predisposition

# **PARTICIPANT SELECTION AND ENROLMENT**

## **5.1 IDENTIFYING PARTICIPANTS**

Only subjects who meet all inclusion and no exclusion criteria can be considered for enrolment in this study. No study-specific procedures can be performed until the patient has signed an informed consent form that has been approved by the Ethics Committee. All patients who are considered for participation in the study should be recorded on a screening log that will be maintained at the site.

- - 1. Identification of Subjects

Patients will only be identified with the full knowledge and co-operation of their Clinical Care Team. Patients will be recruited from the Gynaecological Services of NHS Lothian Hospitals and include those women with uterine fibroids scheduled for hysterectomy.

Potential study recruits will also be identified from the Gynaecological Outpatients Services in NHS Lothian and from the waiting list for women scheduled for hysterectomy for fibroids at NHS Lothian Hospitals.

## **5.2 CONSENTING PARTICIPANTS**

Study participants will be consented by the Study Clinical Investigators and the Clinical Research Fellow. All study participants will receive a detailed patient information sheet with ample opportunity to ask questions about involvement in the study.

## **5.3 SCREENING FOR ELIGIBILITY**

At an initial screening visit the following will be conducted:

1. Medical history recording concomitant medications and menstrual history.
2. Routine physical examination.
3. Recording of vital signs.
4. Clearview hcG™ pregnancy test.
5. Multistix 8 SG™urinalysis.
6. Height and weight measurement with calculation of BMI from the standardised equation kg/m2.
7. The following blood tests: full blood count, urea and electrolytes (including eGFR), liver function tests.

It will be checked that there is no contra-indication to administration of GnRH agonist /antagonist or gadolinium (diabetes/ renal/ hepatic impairment) venepuncture/cannulation and MRI (inability to lie in supine position and claustrophobia) or buscopan, which is given routinely to all patients having a pelvic MRI to enhance image quality.

Each patient must be available throughout the study period.

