## **6.7 OTHER MEDICATIONS**

### **6.7.1 Permitted Medications**

All other medications deemed necessary or standard of care are permitted.

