### **6.7.2 Prohibited Medications**

There are no prohibited medications.

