**4.3 Contraindications**

Zoladex should not be given to patients with a known hypersensitivity to the active substance, to other LHRH analogues, or to any of the excipients of this product.

Zoladex should not be used in pregnancy (see section 4.6).

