**4.6 Pregnancy and lactation**

Pregnancy: Although reproductive toxicity in animals gave no evidence of teratogenic potential, Zoladex should not be used in pregnancy as there is a theoretical risk of abortion or foetal abnormality if LHRH agonists are used during pregnancy. Potentially fertile women should be examined carefully before treatment to exclude pregnancy. Non-hormonal methods of contraception should be employed during therapy and in the case of endometriosis should be continued until menses are resumed.

Pregnancy should be excluded before Zoladex is used for assisted reproduction. The clinical data from use in this setting are limited but the available evidence suggests there is no causal association between Zoladex and any subsequent abnormalities of oocyte development or pregnancy and outcome.

Lactation: The use of Zoladex during breast-feeding is not recommended.

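### The only scheduled pregnancy test is at screening, with no stated limit to first dose; separately, section 6.7 leaves hormonal contraception open despite the attached Zoladex advice

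*Protocol*

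**What the plan says.** **Pregnancy.** The exclusion criteria in Protocol section 4.3 begin with "Pregnant or lactating women". In Appendix 1, section 4.3 of the Zoladex text says "Zoladex should not be used in pregnancy", and section 4.3 of the Cetrotide text lists pregnancy as a contraindication. The check provided is the "Clearview hcG™ pregnancy test" in the screening list of section 5.3. In all six Appendix 4 charts the test stands in the Screening row only. The rows for Visit 1, randomisation and Day 1 carry none, and the main-study Day 1 blood sample covers oestradiol, progesterone, LH and FSH but not hCG.

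No maximum time from test to first dose is given. The ultrasound does have a validity rule, in section 3.1.2: "If Visit 1 falls within 28days of screening then the screening scan will remain valid". Section 4.6 of the Zoladex text says: "Potentially fertile women should be examined carefully before treatment to exclude pregnancy".

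**Contraception.** The same section of the Zoladex text says: "Non-hormonal methods of contraception should be employed during therapy". In the protocol body, sections 4.2 and 4.3 set no contraception requirement. Section 6.7.1 says "All other medications deemed necessary or standard of care are permitted" and section 6.7.2 says "There are no prohibited medications". Section 11 covers the reporting and follow-up of pregnancies, not their prevention.

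**The concern.** There are two separate gaps.

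First, nothing scheduled at dosing confirms that the pregnancy exclusion still holds. The protocol recognises that screening results age, because it gives the scan a 28-day life, but it gives the pregnancy test none. At stake is giving cetrorelix or goserelin to a woman with an unrecognised early pregnancy. Appendix 1 describes the goserelin risk as theoretical, and neither product text reports teratogenicity in animals, but both rule out use in pregnancy.

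Second, a blanket permission for other medication leaves hormonal contraception open alongside goserelin. This is out of step with the attached advice, in a protocol whose section 12.5 relies on Zoladex being used within licence. It also has a scientific cost. The secondary objective in section 2.1.2 asks whether the response depends on hypoestrogenism, and section 9.2 reads the data against hormone profiles from blood and urine. Exogenous hormones could disturb those profiles.

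**Working it through.** The protocol states no test-to-dose interval, so there is no figure of its own to reproduce. An upper limit follows indirectly from other stated windows.

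*Inputs*
- Total participation from screening: up to 20 weeks = 140 days (section 3.2).
- Treatment before surgery: about 12 weeks = 84 days in Group 1, about 13 weeks = 91 days in Group 2 (section 3.1, Main Study).
- Goserelin doses 28 ± 3 days apart; surgery 21 to 28 days after the last dose (section 3.1).
- In Group 2, goserelin starts on Day 7 ± 1, that is 5 to 7 days after Day 1.
- Visit 1 within 28 days of Day 1 (section 3.1.2).

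*Longest time from test to first dose = 140 − (Day 1 to hysterectomy)*
- Group 1, nominal: 140 − 84 = 56 days (8 weeks).
- Group 2, nominal: 140 − 91 = 49 days (7 weeks).
- Group 1, shortest windows: 25 + 25 + 21 = 71; 140 − 71 = 69 days. Longest windows: 31 + 31 + 28 = 90; 140 − 90 = 50 days.
- Group 2, shortest windows: 5 + 71 = 76; 140 − 76 = 64 days. Longest windows: 7 + 90 = 97; 140 − 97 = 43 days.
- Pilot Group A, three doses 28 days apart and surgery at 28 days: 140 − 84 = 56 days. With two doses: 140 − (28 + 28) = 84 days.

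*What else happens in that interval*
- Dosing starts on cycle day 1 to 5, so a new bleed normally follows the test. Main-study women also keep a bleeding diary from Visit 1; the pilot groups do not.
- Every treated woman has a pelvic MRI at Visit 1, no more than 28 days before Day 1.
- If the test-to-dose gap exceeds 28 + 28 = 56 days, Visit 1 must fall more than 28 days after screening. The screening scan has then lapsed and ultrasound is also due at Visit 1.
- None of these is a pregnancy test at dosing. Imaging up to 28 days earlier would miss a very early or later conception. A bleed that is not a true period would still satisfy the cycle-day rule. That such bleeds occur in women with fibroids is an assumption; the protocol gives no rate.

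*Women concerned*
- Trial-allocated drug: 10 + 10 = 20 (Groups 1 and 2). Pilot Group A adds up to 15, whose goserelin is routine care. Group 3 and Pilot Groups B and C receive no study drug.
- For the hormone profiles, one affected woman is 1/10 = 10% of a main-study group.

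**The case against.** The strongest reply on testing is that the schedule already protects against dosing a pregnancy. A new bleed is required, the uterus is imaged within 28 days of Day 1, and any gap above 56 days brings a repeat ultrasound. A reader might take the longer derived gaps (64 to 84 days) as a measure of risk. They are not. The 64 and 69 days in the main study need every dosing and surgery window at its minimum together with the full 20 weeks, and all of these gaps come with fresh imaging. This part of the reply stands. What remains is a small risk of unknown size.

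A reader might also infer that the protocol breaches the Zoladex text. The document does not support that. The text asks for careful examination before treatment and sets no test timing, and screening includes a menstrual history, a physical examination, an hCG test and an ultrasound. Nor does section 11 show that pregnancies were expected: it also mentions partners of male participants in a study of women, so it reads as template wording.

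On contraception, the advice is attached as Appendix 1, the patient information sheet is not shown and may repeat it, and section 6.7.1 covers only medication judged necessary or standard of care. The result is a general permission that does not fit the attached advice, not a direct contradiction. However, an information sheet cannot change what section 6.7.2 allows. Concomitant medication is recorded, so users could be identified, but recording use does not prevent the effect on the hormone profiles. No use of hormonal contraception is documented, so that effect is a possibility only.

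**Conclusion.** Both gaps hold, at modest size. The single scheduled pregnancy test can be about 8 weeks old at first dose in Group 1 and 7 weeks old in Group 2 at nominal treatment lengths. These figures assume that the 20-week cap is counted from screening and is used in full. Cycle timing and Visit 1 imaging reduce the risk of dosing a pregnancy but do not exclude an early one. Sections 6.7.1 and 6.7.2 allow hormonal contraception during goserelin, against the attached advice and to the possible detriment of the secondary hypoestrogenism objective.

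Neither the probability of dosing a pregnancy nor the size of a hormone effect can be estimated from the document. No primary analysis, sample size or power figure changes. The change is advisable because it is cheap and because eligibility checks and permitted medication are fixed in the protocol, not left to an analysis plan.

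**What to change.** 1. Repeat the urine hCG test on Day 1, before the first cetrorelix or goserelin dose, in Groups 1 and 2, and add it to the Day 1 row of those Appendix 4 charts. It is optional before Dose 1 in Pilot Group A, whose goserelin is routine care.
2. State in the protocol that women receiving goserelin use non-hormonal contraception, and amend section 6.7.2 to exclude hormonal contraception during goserelin therapy. As allocation is unknown at enrolment, main-study women would agree to this in case they are allocated to Group 1 or 2. The investigators should decide whether controls need the same limit for the hormone objective.

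Cost: 20 urine tests, or at most 20 + 15 = 35 with Pilot Group A, at a Day 1 contact that is already scheduled, plus a short amendment. The first cetrorelix dose is already given in hospital. A few women may have to change contraceptive method or may decline to take part.

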## **5.4 INELIGIBLE AND NON-RECRUITED PARTICIPANTS**

Ineligible and non-recruited participants will return to routine care and will receive their hysterectomy as planned.

## **5.5 RANDOMISATION**

### **5.5.1 Randomisation**

A randomisation scheme will be drawn up by an independent statistician and allocated treatment codes will be put into sealed consecutively numbered opaque envelopes. When a patient is randomised she will receive the treatment indicated in the next available envelope.

